### Outcome measures

*Primary outcome*
Excess length of stay (eLOS)—a surplus stay of 24 h or more, compared to peer institutions’ Healthcare Resource Groups-predicted length of stay.

*Secondary outcomes*
eLOS or 30-day readmission;In-hospital death or death/readmission within 30 days;Complications of care: hospital-acquired infections and pressure ulcers;Processes of escalation of care: use of the ICU outreach service, admissions to the ICU, and cardiac arrest calls;Staff engagement with the traditional web-based reporting system: number, and type (eg, patient falls or communication failures) of formally reported incidents;Patient safety climate: teamwork and safety subsections of the well validated Safety Attitudes Questionnaire (SAQ).^33^

We believed that tangible improvements in clinical outcomes and quality of care would be mediated by changes in ward processes, and ward safety and teamwork climates. Our chosen outcomes allow us to evaluate this hypothesis. The selected measures are similar to those used in other studies evaluating the quality of ward care,^34^ and have been assessed in a UK setting where appropriate.^33^
Table 1 describes specifically how the components of these outcomes correspond to the study hypotheses outlined earlier.

**Table 1 BMJOPEN2014007510TB1:** Study outcomes and corresponding hypotheses evaluated within the HEADS-UP trial

	Outcome component	Relevant hypothesis	Rationale for outcome selection
Primary outcome	Excess length of stay	Improved clinical outcomes through ward and support service improvements	Length of stay reflects efficient resource use, and possibly quality of care.^35^ Length of stay varies substantially within institutions, with wide differences between the acute admissions unit and downstream wards. Using excess length of stay as an outcome increases study power, facilitating statistical detection of a meaningful change in outcome without requiring an excessive number of wards or data collection period.

Secondary outcomes: clinical outcomes	Mortality	Improved clinical outcomes through ward and support service improvements	Correlates with quality of care^36^ and may relate to performance in non-technical skill domains.^37^
	Readmission	Improved clinical outcomes through ward and support service improvements	Need to confirm that improvements in hospital efficiency do not come at the expense of increased readmissions. 37% of medical readmissions are avoidable,^38^ a proportion that can be reduced with targeted quality improvement initiatives.^39–41^
	Complications of care	Improved situational awareness will mitigate patient risks	Agreement that these outcomes are appropriate patient safety indicators.^42^ Reliable reporting of these outcomes to confirm adherence to stringent centrally mandated targets.^43^ ^44^

Secondary outcomes: processes of care	Escalation of care	Earlier team recognition of the deteriorating patient will facilitate processes underpinning escalation of care	Multidisciplinary interventions, increasing team situational awareness,^45^ may address staff reluctance to appropriately escalate their concerns.^24^ ^46^

Secondary outcomes: staff outcomes	Staff engagement with traditional reporting system	Team-wide recognition of adverse events will improve engagement with existing incident reporting systems	More reports overall, with a lower contribution from reports of slips and falls, are associated with more positive safety culture and risk management ratings.^47^
	Safety and teamwork climate	Empowerment of junior clinicians, with structured communication tool, will improve perceptions of safety and teamwork	Improved safety climate is associated with organisation-wide reduction in adverse events.^48^ SAQ scores previously assessed both in inpatient settings and in the UK.^33^

HEADS-UP, Hospital Event Analysis Describing Significant Unanticipated Problems; SAQ, Safety Attitudes Questionnaire.

### Intervention implementation

#### HEADS-UP implementation at ward level and clinical engagement

Multidisciplinary ward teams will be asked to use HEADS-UP on a daily basis during the normal working week (Monday to Friday). Staffing and service provision are significantly reduced out of hours, and it was not deemed practical to incorporate a HEADS-UP briefing at night or at weekends within those constraints. One of the study leads at each site will supervise the initial use of the tool and answers any questions arising from it. The presence of a researcher will be documented when appropriate.

To maximise clinical engagement with this intervention, we aim to disrupt teams’ existing working patterns as little as possible; they will use HEADS-UP wherever it fits most naturally into their existing schedule. We anticipate that this will ordinarily be early in the day. The HEADS-UP tool itself acts as the written record of the briefing. Its format will remain stable, but further minor changes will be made at the request of individual ward teams to make it responsive to their specific needs. Successful improvement interventions reported elsewhere have adopted a similarly flexible approach.^32^
^49^

Support for the study will be sought from senior clinicians and executives with responsibility for clinical quality, safety and risk management at each site. Presentations to individual clinical teams will publicise the intervention prior to its introduction. No protected time will be available for HEADS-UP training, but the ideal format for each briefing will be discussed in departmental rounds, team meetings and with participating clinicians. The information shared during the daily HEADS-UP briefings may prompt a degree of reflective practice and immediate learning. In addition, a regular summary of the HEADS-UP events recorded from their clinical area will be given to each team. The format of this feedback again depends on the team's existing schedule; where possible, it will be incorporated into existing departmental educational or governance meetings, to place it in the appropriate context and minimise any additional time commitments. This feedback will emphasise the ongoing impact of the information gathered during the HEADS-UP briefings, highlighting any subsequent quality improvement work or changes to support services.

HEADS-UP summaries will also be shared with the governance committees responsible for the issues raised. Clinicians and managers already accountable for quality and safety in these clinical areas will be expected to use the information appropriately to guide resource allocation, and make changes to routine processes or procedures as they see fit. No specific guidance will be issued as to how the HEADS-UP data will be used. We aim to evaluate how, in practice, the intervention will generate changes in clinical services. However, specific safety concerns and significant adverse events raised through HEADS-UP briefings will be emphasised to the responsible clinical team or governance body in order that they take appropriate action.

#### Fidelity of implementation and confounding factors

The quality of HEADS-UP implementation will be evaluated primarily through the daily briefing documentation, recording the team members present, number and type of concerns raised, and the decisions taken as a result. A narrative diary, describing the qualitative impact of HEADS-UP, as well as the downstream quality improvement work and service changes arising from it, will complement the quantitative outcomes. The narrative account will also describe the observation of a number of HEADS-UP briefings, and the extent to which they held true to the perceived ideal in terms of participants, timeliness, focus and intent. The individual, team and organisational barriers and facilitators to the effective implementation of HEADS-UP will be assessed. Together with the objective outcomes listed in table 1, and the staff survey (SAQ) data, this will complete a mixed methods analysis of the HEADS-UP programme.

Staff workload and patient casemix are likely to be the two predominant confounding factors for this non-randomised study. Ward bed occupancy rates will be documented from routine hospital administration systems, and staff perceptions of workload assessed periodically with the validated NASA-Task Load Index (NASA-TLX) tool.^50^ Patient casemix will be tracked with an updated version of the Charlson comorbidity index.^51^
^52^

#### Blinding

Professionals implementing the intervention are not blinded to the ward's assignment group: this is not possible, given the nature of the intervention. Extraction of the clinical outcome measures will be performed primarily by administrative staff not involved in the study (as part of their ordinary duties), who will be blinded to intervention groups.

### Data management

Data will be extracted directly from hospital administrative systems, with a monthly assessment by administrative staff to confirm its reliability. Anonymised data, where appropriate, will be held securely on password-protected hospital intranet systems. Given the nature of the intervention, the time scale of the study, and the extraction of outcomes from existing administrative systems, no data monitoring committee is required. The summarised trial data set will be held by SP, and disseminated to local clinical and managerial healthcare providers as required after the study, with no contractual limitations.

### Sample size, power calculation and analysis

In the 33 months preceding the study, local data from six of the seven anticipated clusters described a median of 522 patients matching our inclusion/exclusion criteria each month (range 316–722). Mean eLOS rates ranged from 5.6% to 51.5%.

Cluster controlled trials also require an estimation of the intraclass correlation coefficient (ICC); this is complex, and observed ICCs rarely match their predicted values. ICC estimation should take into account the results of previous studies, as well as the anticipated numbers of individuals and clusters in the index study. Greater numbers of individuals in a study reduce the width of the ICC confidence interval, mitigating the effect of a relatively small number of clusters.^53^ In addition, clinical outcome measures tend to have lower ICCs than process measures.^53^ The observed ICC for falls in a multifactorial intervention on elderly care wards was only 0.007.^54^ However, ICCs for length of stay and appropriateness of stay in trials of inpatient care pathways were an order of magnitude higher.^55^ We therefore adopted the more conservative ICC estimate of 0.06. In any case, the power under a stepped wedge cluster randomised trial is relatively insensitive to ICC underestimation, compared to a parallel cluster design.^56^ Similarly, stepped wedge trial power is relatively insensitive to variations in the coefficient of variation.^57^ In addition, in our best-case prediction the coefficient of variation approached the level at which adjusting for variable cluster size has a negligible impact on sample size, even in parallel cluster trials.^58^ No adjustment for coefficient of variation was therefore required.

Given the variation in baseline outcomes in our local data set, we then estimated the study's power to detect a 1 standard deviation reduction in eLOS on the wards with the highest and lowest baseline outcome rates. With 7840 patients in the trial (560 patients/month), and two-sided p<0.05, the study would achieve 100% power to detect a 14% absolute risk reduction. At worst, in the ward with the lowest baseline outcome rate, it would achieve 75% power to detect a 2.3% absolute risk reduction. We therefore propose that the study's power to detect a 2–14% absolute risk reduction lies between 75% and 100%. With this complex trial design, statistical uncertainty in power calculations is not unusual. The recent protocol of a large stepped wedge cluster randomised trial similarly produced a range within which its power might lie.^29^ Experts also advocate more widespread recognition of the inherent limitations of statistical power thresholds.^59^

The stepped wedge design compares outcomes in each cluster before and after the introduction of the intervention. Overall differences in outcomes between preintervention and postintervention periods will be reported. Primary analysis will be on an intention-to-treat basis, with a separate prespecified per-protocol analysis of those units implementing the intervention with high fidelity. Analyses will use the patient-level data described above, clustered within ‘units’, using random effects to model the correlation between individuals within the same cluster. Generalised linear mixed models, or generalised estimating equations, will form the basis of the analysis.^57^ Results will also be assessed using a time-to-event regression model. Underlying temporal trends (including seasonal trends) will be accounted for. We will evaluate any interaction effect between intervention group and ‘duration of HEADS-UP implementation’ to see if the intervention exerts an incremental effect over time. There will be a prespecified analysis excluding patients coded for palliative care, to further isolate the effect of the intervention. Sensitivity analyses will judge whether primary outcome results remain unchanged when other patient groups (eg, those spending less than 50% of their stay on the specified ward) are included. No interim analyses are planned, nor is a formal health economics analysis.

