### Study aim and hypotheses

The primary aim of this study is to assess the impact of the HEADS-UP briefing tool on clinically relevant patient outcomes. The secondary aim is to explore how changes in patient outcomes, if any, are mediated by changes in workplace climate and ward processes.

We hypothesised that:
Team use of the HEADS-UP briefing would empower junior clinicians to voice concerns, improving their teams’ situational awareness (an important factor in mitigating risks^19^) and their units’ safety and teamwork climates;This would promote early team recognition of the deteriorating patient, and facilitate the process of escalation of care;Information generated by ward teams would both inform their own practice and prompt downstream service reorganisation;The combination of ward and support service improvement would improve clinical outcomes, with a dose-response relationship (ie, the better the tool is used in practice, the greater the benefit seen);An explicit focus on team-wide recognition of adverse events would improve engagement with existing incident-reporting systems, thus leading to an increase in formally reported incidents within wards implementing HEADS-UP.

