**Figure 3 BMJOPEN2014007510F3:**
[figure not shown]
HEADS-UP (Hospital Event Analysis Describing Significant Unanticipated Problems) stepped wedge cluster design.

The order in which clusters receive the intervention will be guided by logistical restrictions, and the de facto recognition of clinicians enthusiastic to introduce HEADS-UP to their wards. Although cluster randomisation (randomising the order in which the clusters receive the intervention) would be preferable, it is important to recognise the impact of willing early adopters who then lead their colleagues in implementing the intervention.^30^ They are likely to participate more extensively and follow through more rigorously and enthusiastically with the intervention than units at later stages of the intervention diffusion.^31^ Sufficient leadership and support from these early adopters will be needed to maximise the use of HEADS-UP in all the desired areas, much as the introduction of surgical checklists, for instance, has historically relied on strong clinical leadership.^32^ HEADS-UP is introduced to new clusters at two-monthly intervals.

The study is conducted at two sites. The first is a university-associated community general hospital. Clusters from this site are generated from the acute admissions and downstream medical (gastroenterology, respiratory and geriatric) wards. Each cluster comprises clinical areas that are physically linked, served by the same medical team, or both. This will help to limit contamination between groups. The second site is an academic hospital, where HEADS-UP will be implemented within the geriatric wards.

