## Results: pilot implementation

During a 6-week pilot period, participating clinicians honed the format of the HEADS-UP tool, ensuring it could be completed quickly and accurately. Subsequent iterations of the HEADS-UP tool incorporated further feedback from clinical staff and clinical governance teams on the content and use of the HEADS-UP briefing. This largely resulted in an increased focus on the outcomes of the briefing, namely the actions to be taken and which team member would be responsible for them.

The introduction of the tool was supervised initially by a physician researcher (SP). When led by a clinician, the HEADS-UP briefing typically took between 5 and 8 min to complete. Clinical teams’ use of the tool was deliberately unsupervised for the latter half of the pilot period, to gauge whether it was suitably concise and relevant to be used in practice without the presence of the researcher. The HEADS-UP briefing was completed unsupervised on 80% of working days. Taken together, these data suggest that the HEADS-UP trial is feasible.

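### Read naturally, the per-protocol analysis discards the control months of lower-fidelity wards, and no listed analysis tests whether better use of the tool brings greater benefit

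*Protocol article*

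**What the plan says.** The protocol article (Study aim and hypotheses) expects clinical outcomes to improve "with a dose-response relationship (ie, the better the tool is used in practice, the greater the benefit seen").

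Under Fidelity of implementation and confounding factors it says how quality of use is captured: "The quality of HEADS-UP implementation will be evaluated primarily through the daily briefing documentation". What each briefing record holds is also listed there: "recording the team members present, number and type of concerns raised, and the decisions taken as a result". Graded fidelity data will therefore exist for every ward that has switched.

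Under Sample size, power calculation and analysis, the primary analysis is by intention to treat. Two further analyses bear on use of the tool. One is "a separate prespecified per-protocol analysis of those units implementing the intervention with high fidelity". The other concerns elapsed time: "We will evaluate any interaction effect between intervention group and ‘duration of HEADS-UP implementation’ to see if the intervention exerts an incremental effect over time".

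The rollout is not randomised. Under Study design and setting, in the text after Figure 3, the article states: "The order in which clusters receive the intervention will be guided by logistical restrictions". Clinicians' enthusiasm is the other guide it names. Of the early adopters it says: "They are likely to participate more extensively and follow through more rigorously and enthusiastically with the intervention than units at later stages".

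**The concern.** There are two separate problems.

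**Lost control months.** In a stepped wedge, a ward that switches late is a concurrent control for those that switch early. An analysis of the high-fidelity units alone removes the other wards' control months as well as their poorly implemented months. Only the latter are a reason for a per-protocol analysis. Because the article expects fidelity to follow rollout order, the wards most likely to go are the ones that supply the controls. The effect then becomes harder to separate from calendar time, although the same section undertakes to account for temporal and seasonal trends.

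**An untested hypothesis.** The hypothesis concerns a gradient in quality of use. A set restricted to high-fidelity wards has little fidelity contrast left, and the duration interaction measures time since the start. A stated hypothesis therefore has no analysis, although the data are collected. Readers may then take the per-protocol result as evidence for a gradient that it cannot show.

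**Working it through.** **1. Reproducing the stated power.** Inputs from the article: 7 wards, 14 months, two-month steps, 7840 patients, ICC 0.06, lowest baseline rate 5.6%, reduction 2.3 points, two-sided 5%.

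- Patients per ward and two-month period: 7840 / (7 × 7) = 160.
- Total variance: 0.056 × 0.944 = 0.05286. Between wards: 0.06 × 0.05286 = 0.00317. Within a ward-period mean: 0.94 × 0.05286 / 160 = 0.00031.
- The Hussey–Hughes model (random ward intercept, fixed periods) gives SE = 0.00875.
- Power = Φ(0.023/0.00875 − 1.96) = Φ(0.67) = 74.8%. The article states 75%.
- The same model gives 100% for 14 points from 51.5%, as stated.

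**2. Variance when only the earliest k wards are kept.** With ward and period effects and equal cells, the variance of the effect is proportional to 1/SS. For on/off indicator x, K wards and T = 7 periods,

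SS = Σx − Σ(ward totals²)/T − Σ(period totals²)/K + (Σx)²/(KT).

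In the layout where one ward switches in each period, starting with the first:

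- All 7 wards: 28 − 140/7 − 140/7 + 28²/49 = 4.00.
- k = 6: 27 − 139/7 − 127/6 + 27²/42 = 3.33; ratio 4/3.33 = 1.20.
- k = 5: 25 − 135/7 − 105/5 + 25²/35 = 2.57; ratio 1.56.
- k = 4: 22 − 126/7 − 78/4 + 22²/28 = 1.79; ratio 2.24.
- k = 3: 18 − 110/7 − 50/3 + 18²/21 = 1.05; ratio 3.82.

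**3. Range over layouts.** Figure 3 is not available here, so four layouts were assumed: the one above, and three in which all wards are unexposed in the first period and two wards share the last, the first or a middle step. Least squares gives these variances relative to all seven wards:

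| Earliest wards kept | Those wards only | Plus all wards' control months | Avoidable loss |
|---|---|---|---|
| 3 | 3.6–6.8 | 1.6–2.4 | see below |
| 4 | 2.2–2.9 | 1.2–1.6 | see below |
| 5–6 | – | – | about 1.1–1.6-fold |

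For three or four wards, the loss within the same layout is 1.4–3.2-fold, and 6–10 of the 14 months have no retained ward in the control state. A random ward intercept with ICC 0.06 gives nearly the same ratios.

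**4. In terms of power.** In the worst case of step 1, the four earliest wards alone have an SE 1.50 times larger: Φ(0.023/(1.50 × 0.00875) − 1.96) ≈ 42%. Keeping the other wards' control periods gives 56–66%, depending on whether the first ward starts in period 1 or 2.

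**5. What a test of dose-response needs.** Let F be the post-switch fidelity score.

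- A single exposure D = x·F, set to 0 before the switch, does not isolate a gradient. If F = c on every ward, D = c·x, and its test statistic is exactly that of the on/off effect.
- In simulation with a flat 2.3-point effect and no gradient (baseline 5.6%, 7840/(7 × 14) = 80 patients per ward-month), the slope on D was significant in about 62–71% of runs.
- The coefficient of D with x also in the model was significant in no more than about 5%. That coefficient is the test.
- Its power is about 9–22%, for assumed fidelity between 0.4 and 1.0 and a linear effect reaching 2.3 points at full fidelity. It cannot be estimated if fidelity is the same on all wards.

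**The case against.** The per-protocol plan is one condensed clause. It does not say that other wards' control months are dropped, and the data set and fidelity threshold are commonly left to an analysis plan, which is not shown. This is fair: the missing threshold is not part of the point, and the precision loss holds only on the natural reading. If that reading is not intended, one sentence settles it.

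A reader might infer that the subset loses all its concurrent controls, or that the effect cannot be estimated. The article does not support that. Retained wards with staggered starts control for each other until the last one switches. Estimation fails only with a single ward, or with two that share a step under categorical period effects; the article specifies neither that layout nor that form of time adjustment. Nor does it say how few wards will qualify, and with five or six the loss is modest.

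A reader might also infer that selecting on fidelity makes the estimate reflect better wards. Stable differences between wards are largely removed by the before–after comparison within each ward, and any fidelity analysis uses the same non-randomised behaviour.

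A single fidelity exposure on all wards is a tempting remedy. Its power looks better, at 49–62% under the assumed patterns, but most of that is the on/off effect, so a positive slope would not show dose-response. The pilot figure ("The HEADS-UP briefing was completed unsupervised on 80% of working days") is likewise a feasibility result for how often the briefing was done, not a threshold for quality of use.

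Finally, the analysis is secondary. That limits the consequence but leaves the mismatch between hypothesis and analysis.

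**Conclusion.** The point holds in two parts.

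First, on the natural reading, the per-protocol analysis gives up precision without need. The avoidable variance loss is 1.4–3.2-fold if the earliest three or four wards qualify, and about 1.1–1.6-fold if five or six do. This rests on equal ward sizes, categorical period effects, the four assumed layouts and fidelity following rollout order, as the article expects.

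Second, and independent of those assumptions, no stated analysis relates outcome to graded quality of use, although this is a stated hypothesis. Seven wards will support only a weak, exploratory answer.

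The intention-to-treat analysis and its stated power are not in question.

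**What to change.** 1. Fit the per-protocol analysis on all seven wards. Keep every ward's pre-switch months and exclude only the post-switch data of units that do not meet a fidelity criterion fixed before analysis.
2. Add an exploratory dose-response analysis in the primary model on all wards. Keep the on/off term and add a post-switch ward-month fidelity score built from the daily briefing records: completion, team members present, concerns raised and decisions taken. State that the test is the fidelity coefficient given on/off status.
3. Report both beside the unchanged intention-to-treat analysis. State that fidelity is not randomised and is tied to rollout order, that power for the gradient is low, and that it cannot be estimated if fidelity does not vary.

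The cost is analysis wording and the construction of a score from records already being collected. The article reports data collection as ongoing, so both can be fixed before analysis.

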**Methods/analysis:**

7 wards from 2 hospitals will progressively incorporate the intervention into daily practice over 14 months. Wards will adopt HEADS-UP in a pragmatic sequence, guided by local clinical enthusiasm. Initial implementation will be facilitated by a research lead, but rapidly delegated to clinical teams. The primary outcome is excess length of stay (a surplus stay of 24 h or more, compared to peer institutions’ Healthcare Resource Groups-predicted length of stay). Secondary outcomes are 30-day readmission or excess length of stay; in-hospital death or death/readmission within 30 days; healthcare-acquired infections; processes of escalation of care; use of traditional incident-reporting systems; and patient safety and teamwork climates. HEADS-UP will be analysed as a stepped wedge cluster controlled trial. With 7840 patients, using best and worst case predictions, the study would achieve between 75% and 100% power to detect a 2–14% absolute risk reduction in excess length of stay (two-sided p<0.05). Regression analysis will use generalised linear mixed models or generalised estimating equations, and a time-to-event regression model. A qualitative analysis will evaluate facilitators and barriers to HEADS-UP implementation and impact.

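### With a non-randomised roll-out order, ward fixed effects would keep the primary estimate within wards at almost no cost; the bias they remove is small under the models named

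*Protocol article*

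**What the plan says.** Under Study design and setting the start order is "guided by logistical restrictions, and the de facto recognition of clinicians enthusiastic to introduce HEADS-UP to their wards". The same paragraph concedes the alternative: "Although cluster randomisation (randomising the order in which the clusters receive the intervention) would be preferable". The abstract gives the scale, "7 wards from 2 hospitals will progressively incorporate the intervention into daily practice over 14 months", and the steps are two months apart ("HEADS-UP is introduced to new clusters at two-monthly intervals").

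Under Sample size, power calculation and analysis, the historical data from six of the seven wards are summarised as "Mean eLOS rates ranged from 5.6% to 51.5" per cent. The section describes the design as a before/after comparison in each cluster. The analysis is then to be clustered within units, "using random effects to model the correlation between individuals within the same cluster", and "Generalised linear mixed models, or generalised estimating equations, will form the basis of the analysis". Temporal and seasonal trends will be adjusted for. Ward is not named as a fixed effect.

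**The concern.** A random ward intercept, or GEE without ward terms, combines two comparisons. One is each ward against itself before and after its start. The other is wards with long exposure against wards with short exposure. The second is free of bias only if ward level is unrelated to start time. Randomising the order would secure that, and this trial does not randomise it.

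The wards differ widely in baseline rate and include an admissions unit as well as downstream specialty wards. If low-rate wards happened to start first, the between-ward part would look like benefit; if high-rate wards started first, it would look like harm. The analysis would then not be purely the within-ward comparison that the article describes.

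**Working it through.** **Inputs.** From the article: 7 wards, 14 months, two-month steps, 7840 patients (560 per month, so 80 per ward-month), ICC 0.06, two-sided 0.05, ward rates 5.6% to 51.5%, worst-case target 2.3 points. Assumed: equal ward sizes, even spacing of the seven rates, a linear (risk-difference) scale, and period effects in the model. The design figure is not available, so two layouts are used: 7 periods × 160 patients per ward, and 8 periods × 140.

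**Step 1: reproduce the stated power.** The Hussey–Hughes variance is

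Var = Iσ²(σ² + Tτ²) / [(IU − W)σ² + (U² + ITU − TW − IV)τ²].

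Here X is the 0/1 exposure of each ward in each period, U its total, W the sum of squared period totals, and V the sum of squared ward totals.

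- Seven periods: I = T = 7, U = 28, W = V = 140, so IU − W = 56 and the last bracket is 784 + 1372 − 980 − 980 = 196.
- At a rate of 5.6%, p(1 − p) = 0.05286; σ² = 0.94 × 0.05286/160 = 0.0003106; τ² = 0.06 × 0.05286 = 0.003172.
- Var = 7.66 × 10⁻⁵, SE = 0.875 points, power = Φ(2.3/0.875 − 1.96) = 74.8%. The article states 75%.
- The 8-period layout gives 74.0%. The 14-point case gives 100% in both.

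**Step 2: ward fixed effects.** Let τ² go to infinity. Seven periods: Var = 49σ²/196 = σ²/4 = 7.76 × 10⁻⁵, SE 0.881 points, power 74.2%. Eight periods: 73.6%. At ICC 0.06 the variance rises by 1.4% and 1.1%, and power falls by 0.6 and 0.4 points.

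**Step 3: weight on the between-ward comparison.** The random-intercept estimate is (1 − w) × within + w × between, with w = 1 − Var(random)/Var(fixed). Write ρ = τ²/σ² = m × ICC/(1 − ICC), with m patients per ward-period. Then w = 1/(2 + 7ρ) for seven periods and w = 7/(16 + 72ρ) for eight.

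**Step 4: worst-case between-ward slope with no true effect.** Evenly spaced rates lie (51.5 − 5.6)/6 = 7.65 points apart. In strict rate order, neighbouring wards differ in share of time exposed by 1/7 or 1/8. The slope is therefore 7.65 × 7 = 53.55 points, or 7.65 × 8 = 61.2 points.

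**Step 5: ICC implied by these rates.** The variance of the seven rates is 0.0273 and the mean of p(1 − p) is 0.1806, so the ICC is 0.0273/(0.0273 + 0.1806) = 0.13.

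**Step 6: bias = w × slope.**

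| Correlation used | w (7 / 8 periods) | Bias, points | Bias/SE |
|---|---|---|---|
| ICC 0.13 | 0.58% / 0.45% | 0.31 / 0.28 | 0.19 / 0.17 |
| ICC 0.06 | 1.36% / 1.06% | 0.73 / 0.65 | 0.42 / 0.37 |
| Independence (ICC 0) | 50% / 43.75% | 26.8 / 26.8 | not shown |
| Ward fixed effects | 0 | 0 | 0 |

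The SE is about 1.66 to 1.74 points, taking total variance at the mean rate (0.2855 × 0.7145 = 0.204). Averaged over random orders at ICC 0.13, the absolute shift is about 0.1 point. Simulated REML and exchangeable GEE fits differed from fixed effects by about 0.3 points. The variance cost at ICC 0.13 is 1/(1 − w) − 1, or 0.5% to 0.6%.

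**The case against.** With about 1,120 patients per ward, a random-intercept estimate is already almost the within-ward estimate, and a mixed model or exchangeable GEE estimates the correlation from the data. Wards that differ enough to confound also raise the estimated ICC and shrink the leak. This stands, and it is why 0.3 points is the better figure.

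Three stronger readings are tempting, and the article does not support them:

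- **The two model families could differ by some 27 points.** That figure belongs to GEE with independence working correlation and no ward terms. The article does not name it, and it fits poorly with the statement that within-cluster correlation is modelled. The working correlation is also a detail commonly left to an analysis plan.
- **The bias is about 30% of the target effect.** This divides 0.65 to 0.73 by 2.3 points. It pairs a planning ICC of 0.06 with rates that imply about 0.13, and 2.3 points is the target for the lowest-rate ward only, near the bottom of the stated 2 to 14 point range.
- **Enthusiasm is confounded with baseline excess stay.** No passage links them. Strict rate ordering and even spacing are constructions made to bound the problem.

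The article also calls the study non-randomised, names workload and casemix as the main confounders and plans to record both. That is to its credit, but it does not remove stable ward differences from the between-ward part of the estimate.

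**Conclusion.** The point holds as a minor one. The order is not randomised, and the named models use some between-ward information that only an unrelated order would justify. The consequence is bounded at about 0.3 points (under 0.2 SE) when the correlation matches the ward spread, and about 0.7 points (about 0.4 SE) if the ICC were 0.06. Both figures assume the most adverse ordering, even spacing, equal ward sizes and a linear scale. The plan as written should not be read as producing a seriously biased primary result. The case for change is that a bias of unknown sign can be set to zero for very little.

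**What to change.** State in the analysis section that the primary model includes ward (six indicator terms) and calendar period as fixed effects, whichever model family is kept. The effect is then the within-ward comparison that the article describes. Report the random-ward model as a sensitivity analysis.

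This is a change of wording only. It costs about 0.5% to 1.4% more variance, or 0.4 to 0.6 power points in the worst-case scenario, and it limits inference to these seven wards rather than a wider population of wards. It removes stable ward differences only. Ward-specific trends, changing casemix and a larger effect in enthusiastic early wards remain, and the report should say so.
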